#### i) Effectiveness outcomes

The effectiveness of the complex multiple risk behaviour intervention in comparison with the usual care at maximum 12 months post-intervention will be measured by:
*Primary outcome measures*
Positive change in baseline eating behaviour: adherence to the Mediterranean dietary pattern in low adherence people. For the evaluation, the 14-item Questionnaire of Mediterranean diet adherence (PREDIMED study) will be used [49]. The positive change has been defined as obtaining eight or fewer points at the study entry and nine or more at the end of the study in this questionnaire.Positive change in baseline physical activity behaviour: sufficient physical activity level in insufficiently active people. For the evaluation, the International Physical Activity Questionnaire will be used [50]. The positive change has been defined as having a low physical activity level at the study entry and a moderate or high physical activity levelat the end of the study.Positive change in baseline smoking behaviour: self-reported continuous abstinence [51]. For the evaluation, the interview will be used and optionally the cooximetry. The positive change has been defined as smoking at the study entry and not smoking at the end of the study. We will measure the punctual and continuous abstinence at these two times.

*Secondary outcome measures*

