### Assignment of intervention

The allocation schedule for random assignment of intervention to PHC centres will be computer generated at a central location (IDIAP Jordi Gol, Barcelona, Spain). For each of the seven Spanish Autonomous Communities, we will randomly allocate half of the PHC centres to the intervention group and the other half to the control group. In total, 13 PHC centres will be allocated to the intervention group and 13 other to the control group. The allocation will not be concealed at PHC centres and no blinding will be done.

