### Data collection and management

Data will be collected at PHC centre, professional and participant levels. Data collection methods and procedures are summarised in Table 4.

**Table 4 Tab4:** Schedule of Data Collection Methods and Procedures

			Pre-implementation/Pre-study consent/screening	During implementation			Post-implementation
Activity/Assessment	Data collection	Responsible		Study baseline	Intervention visits	Follow-up 12-months	
PHC centre level							
Characteristics of assigned people	Form report	Research team each autonomous community	x				
Organisational structure	Form report	Research team each autonomous community	x				
Survey of Organizational Attributes for Primary Care	Self-administered questionnaire	Research team each autonomous community	x				x
Professional level							
Age, sex, academic education and experience in PHC	Self-administered questionnaire	Research team each autonomous community	x				
Daily consumption of fruits and vegetables/Level of physical activity/Smoking behaviour	Self-administered questionnaire	Research team each autonomous community	x				x
Appropriateness and acceptability	Self-administered questionnaire	Research team each autonomous community	x				x
Determinants of implementation (CFIR constructs)	Focus group	Research team each autonomous community					x
Participant level							
Informed consent	Paper document	PHC professionals	x				
Age and sex	CRF	PHC professionals	x				
Screening unhealthy behaviours	CRF	PHC professionals	x				
Inclusion/Exclusion criteria	CRF	PHC professionals	x				
Adherence to the Mediterranean dietary pattern	CRF (14-item Questionnaire of Mediterranean diet adherence	External unit of local trained personnel		x		x	
Quality of diet	CRF (Diet Quality Index-International)	External unit of local trained personnel		x		x	
Physical activity behaviour	CRF (International Physical Questionnaire)	External unit of local trained personnel		x		x	
Smoking behaviour	CRF (interview and optional cooximetry)	External unit of local trained personnel		x		x	
Stage of change	CRF	PHC professionals (intervention group)		x		x	
		External unit of local trained personnel (control group)		x		x	
Health-related quality of life	CRF (EuroQol-5D questionnaire)	External unit of local trained personnel		x		x	

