At PHC centre level, we will collect information related to: assigned population (total number; average age; distribution by age group and sex; percentage of immigrants; deprivation index; prevalence of tobacco use; level of physical activity and number of people allocated to home care), organisational structure (population coverage; average attendance; number of physicians, nurses and social workers; accreditation as training health centre; participation in undergraduate and postgraduate training; average visits per day; population per health professional; average time per visit and participation research experience). We will also measure the PHC centres’ internal resources for change by the “Survey of Organizational Attributes for Primary Care” [70].

At the professional level, personal data will be collected (age, sex, academic education and experience in PHC). PHC professionals will have to complete a self-administered questionnaire. This questionnaire collects information about professionals’ behaviours with reference to tobacco use, daily consumption of fruit and vegetables and level of physical activity. In addition only in health professionals of intervention centres, it includes nine items to measure the perception of appropriateness and acceptability of the intervention; these items are based in questionnaires which measure similar constructs [71].

Participant-level data are described in Table 4. Recruitment, first screening for entrance to the study and intervention visits will be done by health professionals. Data collection at participant level will be supported by an external unit of local trained personnel who will carry out two visits (baseline and at the 12 months) in each PHC centre because they are not considered as usual care tasks. Data will be collected by means of an online CRF specially designed for the study. This CRF will be pilot tested in pre-implementation stage (see Table 3). The management of the study is based on a central coordination unit, a regional coordination unit and a PHC coordination unit using different periodic communication methods (meetings, teleconferences, e-mails, etc.).

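### Blinding is ruled out for everyone, including the external unit that collects all three self-reported primary outcomes and has no stated treatment role

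*Protocol article*

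**What the plan says.** The section on assignment of intervention in the protocol article excludes masking outright: "The allocation will not be concealed at PHC centres and no blinding will be done". No role is exempted and no reason is given.

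The section on data collection and management separates treating staff from assessing staff. On the treating side: "Recruitment, first screening for entrance to the study and intervention visits will be done by health professionals". On the assessing side: "Data collection at participant level will be supported by an external unit of local trained personnel who will carry out two visits", one at baseline and one at 12 months.

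Table 4 names the external unit as responsible at both visits, in both arms, for:
- diet: "CRF (14-item Questionnaire of Mediterranean diet adherence";
- physical activity: "CRF (International Physical Questionnaire";
- smoking behaviour, by interview with optional cooximetry;
- several secondary measures, including the PHQ-9, the GAD-7 and the CIDI.

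The effectiveness outcomes section turns each primary measure into changed or not changed. Diet counts as changed on "obtaining eight or fewer points at the study entry and nine or more at the end of the study". Activity must move from low to moderate or high, and smoking from smoker to non-smoker. On verifying smoking it says: "For the evaluation, the interview will be used and optionally the cooximetry".

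Two further rows of Table 4 matter. Stage of change is rated by the centre's professionals in the intervention group but by the external unit in the control group. The resource-use row, also the unit's task, includes group sessions attended and community resources used.

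**The concern.** Participants and treating professionals cannot reasonably be masked to an intervention of this kind, and nobody would expect it. The external unit is different: the article gives it no part in delivering the intervention and no reason to know the allocation.

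The outcomes it records are open to influence. A single diet point, one activity category or one answer about smoking moves a participant from failure to success, and only smoking has a biochemical check, which is optional. If assessors know the arm, the way they put questions, clarify answers or code them can differ between arms. Such an error goes straight into the estimated difference. The hierarchical models and multiple imputation in the analysis section handle clustering and missing data; they do not correct measurement that differs by arm.

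**Working it through.** **1. Roles set side by side**

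| Question | What the article gives |
|---|---|
| Who treats? | The centre's professionals |
| Who records the three primary outcomes? | The external unit, both arms, baseline and 12 months |
| Does the unit have a treatment role? | None stated |
| Is the unit masked? | No; blinding is excluded without exception |
| Does its task list reveal the arm? | Yes: it rates stage of change only in control centres, and it asks about group sessions and community resources |

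The conclusion rests on this comparison. No figure in the article decides it.

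**2. The plan's own figures**

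The sample-size section gives 140 participants per centre, 13 centres per arm, 30% loss, an intracluster correlation of 0.01 and a difference of 8 percentage points in positive change in one or more behaviours.
- Totals: 26 × 140 = 3640 and 13 × 140 = 1820, as stated.
- Expected analysed per centre: 140 × 0.70 = 98.
- Design effect: 1 + 97 × 0.01 = 1.97.
- Effective number per arm: 13 × 98 / 1.97 ≈ 647.

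The control rate is not given, so it has to be assumed below.

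**3. Illustration of scale (assumed inputs)**

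Let p be the true rate of positive change in the intervention arm and f the share of its true non-changers recorded as changers, with no such error in the control arm. The added difference is f × (1 − p).

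With no true effect, p equals the control rate. At an assumed 30%:
- f = 2%: 0.02 × 70 = 1.4 points
- f = 5%: 0.05 × 70 = 3.5 points
- f = 10%: 0.10 × 70 = 7.0 points

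If the 8-point effect is real, p = 38%, and f = 5% adds 0.05 × 62 = 3.1 points.

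Varying the assumed control rate at f = 5% with no true effect, and using 647 effective participants per arm:

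| Control rate | Added difference (points) | Chance of a significant result favouring the intervention |
|---|---|---|
| 20% | 0.05 × 80 = 4.0 | 41% |
| 30% | 0.05 × 70 = 3.5 | 27% |
| 46% | 0.05 × 54 = 2.7 | 16% |

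The nominal chance is 2.5% (two-sided 5%; the article does not state sidedness).

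**The case against.** **Mode of administration.** A reader might infer that all three primary outcomes are taken by interview. The article says so only for smoking. Diet and activity are listed as CRF questionnaires under the external unit; because other Table 4 rows are labelled self-administered, interviewer administration is a fair inference, but it is not stated. Fixed items with preset cut-offs also leave an assessor less room than an open interview. This stands, and it weakens the mechanism for two of the three outcomes.

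**Cost.** A reader might also infer that masking costs nothing because the unit already exists. The stage-of-change row does not support that: an identical form in both arms means giving the unit a task it does not now have in intervention centres. In those centres the professional's rating also guides which intervention is given, so it cannot simply be moved. This stands, and the fix has to allow for it.

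**Strength of masking.** Whole centres are allocated, allocation is open there, the assessors are local and visit the centres, and workshops are held on site. One disclosure unmasks a centre. Taking arm-revealing items last protects the interview in progress but not later participants at the same centre. This stands: masking would be partial.

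**The other bias.** Participants know what care they receive and supply all three outcomes themselves. Masking assessors leaves their own over-reporting untouched. This also stands.

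**Pragmatic aim.** The article openly describes a hybrid trial meant to work with its context rather than control it. That explains unmasked clinicians and participants. It does not explain telling the allocation to assessors who need not know it.

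**Conclusion.** The point holds as a design weakness that can be reduced, not as a contradiction or a numerical error. The article excludes masking for assessors who record self-reported, dichotomised primary outcomes in both arms and have no stated part in treatment, and it gives them tasks that reveal the arm. It should be amended.

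The size cannot be established from the article. The 1.4, 3.5 and 7.0 points rest on an assumed 30% control rate, assumed misrecording rates, error in one direction in one arm only, and no true effect; at 5% misrecording the figure is about 3.1 points if the 8-point effect is real. A reader might take 3.5 points as what masking would save. The documents do not support that: no misrecording rate is given, masking would be incomplete, and participants' own reporting bias would persist. The figures show only that modest differential error would matter beside an 8-point target.

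**What to change.** Amend the section on assignment of intervention, and Table 4 to match:
- State that participants and treating professionals are unblinded, but that external-unit assessors are not told the centre's allocation.
- Ask participants not to disclose their care to the assessor.
- Complete the three primary instruments and the CIDI before any item that reveals the arm, in particular group sessions attended and community resources used.
- Have the unit record stage of change for the outcome at the end of the visit, on the same form in both arms. Leave unchanged the professionals' own assessment used to deliver the intervention.
- Have assessors record at the 12-month visit which arm they believe the centre is in, so that the success of masking can be reported.

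The cost is a short amendment, assessor instructions, a revised form order and a few extra items per intervention participant. The existing unit already makes both visits in both arms, so no further visits are implied. Masking will be partial, and the report should say so.

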### Data collection and management

Data will be collected at PHC centre, professional and participant levels. Data collection methods and procedures are summarised in Table 4.

**Table 4 Tab4:** Schedule of Data Collection Methods and Procedures

			Pre-implementation/Pre-study consent/screening	During implementation			Post-implementation
Activity/Assessment	Data collection	Responsible		Study baseline	Intervention visits	Follow-up 12-months	
PHC centre level							
Characteristics of assigned people	Form report	Research team each autonomous community	x				
Organisational structure	Form report	Research team each autonomous community	x				
Survey of Organizational Attributes for Primary Care	Self-administered questionnaire	Research team each autonomous community	x				x
Professional level							
Age, sex, academic education and experience in PHC	Self-administered questionnaire	Research team each autonomous community	x				
Daily consumption of fruits and vegetables/Level of physical activity/Smoking behaviour	Self-administered questionnaire	Research team each autonomous community	x				x
Appropriateness and acceptability	Self-administered questionnaire	Research team each autonomous community	x				x
Determinants of implementation (CFIR constructs)	Focus group	Research team each autonomous community					x
Participant level							
Informed consent	Paper document	PHC professionals	x				
Age and sex	CRF	PHC professionals	x				
Screening unhealthy behaviours	CRF	PHC professionals	x				
Inclusion/Exclusion criteria	CRF	PHC professionals	x				
Adherence to the Mediterranean dietary pattern	CRF (14-item Questionnaire of Mediterranean diet adherence	External unit of local trained personnel		x		x	
Quality of diet	CRF (Diet Quality Index-International)	External unit of local trained personnel		x		x	
Physical activity behaviour	CRF (International Physical Questionnaire)	External unit of local trained personnel		x		x	
Smoking behaviour	CRF (interview and optional cooximetry)	External unit of local trained personnel		x		x	
Stage of change	CRF	PHC professionals (intervention group)		x		x	
		External unit of local trained personnel (control group)		x		x	
Health-related quality of life	CRF (EuroQol-5D questionnaire)	External unit of local trained personnel		x		x	
Number in the last 12 months of: hospital care (emergency visits and stays), secondary care (visits to specialists), primary care (visits to physician and nurse), social care services (visits to social worker), outpatient diagnostic tests, medication use, group sessions attended, community resources used and loss of productivity (days off work).	CRF Computerised pharmacy records Electronic health record	External unit of local trained personnel		x		x	
Body mass index, waist circumference, blood pressure and lipid profile	CRF	External unit of local trained personnel		x		x	
Cardiovascular risk	CRF (REGICOR and SCORE function charts)	External unit of local trained personnel		x		x	
Arterial stiffness	CRF (measured by the Vascular Screening System VaSera VS-1500 N or VaSera VS-2000)	External unit of local trained personnel		x		x	
Ankle-brachial index	CRF (measured by the Vascular Screening System VaSera VS-1500 N or VaSera VS-2000)	External unit of local trained personnel		x		x	
Functional social support	CRF (questionnaire Duke-UNC-11)	External unit of local trained personnel		x		x	
Risk of depression	CRF (algorithm PredictD)	External unit of local trained personnel		x		x	
Anxiety	CRF (General Anxiety Disorder-7 questionnaire)	External unit of local trained personnel		x		x	
Depression	CRF (Patient Health Questionnaire-9 and the Composite International Diagnostic Interview	External unit of local trained personnel		x		x	
Appropriateness and acceptability of intervention	Self-administered questionnaire	PHC professionals intervention group			x	x	
Determinants of implementation (CFIR constructs)	Focus group	Research team each autonomous community					x

*CFIR* Consolidated Framework for Implementation Research, *CRF* Case Report Form, *PHC* Primary Health Care

At PHC centre level, we will collect information related to: assigned population (total number; average age; distribution by age group and sex; percentage of immigrants; deprivation index; prevalence of tobacco use; level of physical activity and number of people allocated to home care), organisational structure (population coverage; average attendance; number of physicians, nurses and social workers; accreditation as training health centre; participation in undergraduate and postgraduate training; average visits per day; population per health professional; average time per visit and participation research experience). We will also measure the PHC centres’ internal resources for change by the “Survey of Organizational Attributes for Primary Care” [70].

At the professional level, personal data will be collected (age, sex, academic education and experience in PHC). PHC professionals will have to complete a self-administered questionnaire. This questionnaire collects information about professionals’ behaviours with reference to tobacco use, daily consumption of fruit and vegetables and level of physical activity. In addition only in health professionals of intervention centres, it includes nine items to measure the perception of appropriateness and acceptability of the intervention; these items are based in questionnaires which measure similar constructs [71].

Participant-level data are described in Table 4. Recruitment, first screening for entrance to the study and intervention visits will be done by health professionals. Data collection at participant level will be supported by an external unit of local trained personnel who will carry out two visits (baseline and at the 12 months) in each PHC centre because they are not considered as usual care tasks. Data will be collected by means of an online CRF specially designed for the study. This CRF will be pilot tested in pre-implementation stage (see Table 3). The management of the study is based on a central coordination unit, a regional coordination unit and a PHC coordination unit using different periodic communication methods (meetings, teleconferences, e-mails, etc.).

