### Intervention

The intervention is based on the Transtheoretical Model (TTM) [32, 33] and will be made by physicians and nurses in the routine care of PHC practices according to the conceptual framework of the “5A’s”: Assess, Advise, Agree, Assist, and Arrange-follow up [34]. It will consist of a first visit of screening in which PHC professional will assess person level of behaviour and stage of change (“Assess”). Behaviours will be assessed by one question to know tobacco use during the last month, two validate questions about the daily consumption of fruits and vegetables [35] and the Brief Physical Activity Assessment Tool [36, 37]. Stages of change will be assessed on the basis of core constructs of the TTM for each of the target behaviours (see Table 1) [32]. Subsequently, the PHC professional will advise the person (“Advise”), will agree with him/her on a realistic set of goals (“Agree”), will assist to anticipate barriers and will develop a specific action plan (“Assist”), and will arrange follow-up support (“Arrange”).

**Table 1 Tab1:** Core constructs of the Transtheoretical Model (Prochaska et al. 2008) [32]

Stages of Change	Description
Precontemplation	No intention to take action within the next 6 months
Contemplation	Intends to take action within the next 6 months
Preparation	Intends to take action within the next 30 days and has taken some behavioural steps in this direction
Action	Changed overt behaviour for less than 6 months
Maintenance	Changed overt behaviour for more than 6 months
Termination	No temptation to relapse and 100% confidence

Intervention is based on the results of previous phases (preclinical, phase I and phase II) [23–25, 38–42]. It will have a maximum duration of 12 months and it will be carried out to three different levels (individual, group and community) according to stages of change and unhealthy behaviour (see Table 2). It will focus on all three target behaviours and PHC professional together with the participant will develop priority actions on one or more of these behaviours.

**Table 2 Tab2:** Description of intervention

	Unhealthy behaviours								
	Tobacco use			Insufficient physical activity			Non-adherence to Mediterranean dietary pattern		
Level of intervention	Individual	Group	Community	Individual	Group	Community	Individual	Group	Community
Stages of change									
Precontemplation	Very brief intervention + SMS			Very brief intervention + SMS			Very brief intervention + SMS		

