Beginning or making a behaviour change. The proportion of people who are in the stages of action, maintenance or termination according to the TTM at the study entry and at 12 months.Change from baseline on sedentary behaviour. It will be measured by the sitting items from the International Physical Activity Questionnaire.Change from baseline on diet quality. Diet Quality Index-International will be used to determine diet quality [52].Change from baseline on health-related quality of life. It will be measured by the EuroQol-5D questionnaire [53].Reduction of the cardiovascular risk. The proportion of people with low/moderate and high/very high baseline cardiovascular risk who have reduced it. Cardiovascular risk will be calculated using REGICOR [54, 55] and SCORE [56] function charts.Change from baseline on body mass index. Body mass index is defined as the body weight divided by the square of the body height and is expressed in units of kg/m^2^.Change from baseline on waist circumference. The waist circumference will be measured at a level midway between the lowest rib and the iliac crest. It will be expressed in units of cm.Change from baseline on blood pressure. It will be measured in the routine clinical practice by validated electronic monitors and it will be expressed in units of mmHg.Change from baseline on lipid profile. The lipid profile will include: low-density lipoprotein, high-density lipoprotein, triglycerides and total cholesterol. They will be expressed in units of mg/dl.Change from baseline on arterial stiffness. Arterial stiffness will be assessed by the “Cardio-Ankle Vascular Index”. It will be measured by the Vascular Screening System VaSera VS-1500 N or VaSera VS-2000.Change from baseline on theankle-brachial index. It will be measured by the Vascular Screening System VaSera VS-1500 N or VaSera VS-2000.Change from baseline on the “REgicor and Artper Score fOr aNkle brachial index (REASON)” [57].Change from baseline on the perceived functional social support. The questionnaire Duke-UNC-11 will be used to determine the perceived functional social support [58–60].Reduction of the incidence of major depression will be evaluated by CIDI interview [61].Reduction of the risk of depression in participant non-depressed at baseline. Risk of depression will be calculated using the algorithm PredictD [62].Reduction of depression symptoms. The Patient Health Questionnaire-9 will be used to determine the prevalence and the severity of depression symptoms [63].Reduction of anxiety symptoms. The General Anxiety Disorder-7 questionnaire will be used to determine the prevalence and the severity of anxiety symptoms [64].Change from baseline on unhealthy behaviours of professionals of the PHC intervention centres.

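### Stage of change is scored by the treating staff in the intervention arm and by external staff in the control arm, so a rater effect that emerges by 12 months cannot be told apart from the intervention effect on one secondary outcome

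*Protocol article*

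**What the plan says.** Under Data collection and management, Table 4 lists two responsible parties for stage of change: "PHC professionals (intervention group") and "External unit of local trained personnel (control group"). Both rows are marked at study baseline and at the 12-month follow-up. The source is given only as the case report form.

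Under Effectiveness outcomes, the first-listed secondary measure is the proportion of "people who are in the stages of action, maintenance or termination according to the TTM", taken at study entry and at 12 months.

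The Intervention section says the intervention "will be made by physicians and nurses in the routine care of PHC practices". It also makes staging part of the treatment encounter: at the first visit the "PHC professional will assess person level of behaviour and stage of change". Assignment of intervention states that there is no blinding and that allocation is not concealed at the centres.

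Two neighbouring items are worded in ways that invite comparison. Blood pressure is described under the secondary outcomes as follows: "It will be measured in the routine clinical practice by validated electronic monitors". Table 4, however, makes the external unit responsible for it. The last secondary outcome is "Change from baseline on unhealthy behaviours of professionals of the PHC intervention centres".

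**The concern.** A randomised comparison needs the outcome to be obtained in the same way in both arms. Here the type of assessor is fixed by the arm. In the intervention centres, the staff group that agreed goals and an action plan with the participant also records whether the participant has reached the action stage. The participant gives the answer to a clinician with whom there is a relationship; the Background itself remarks that users tend to trust their primary care professionals. In the control centres, an outside data collector asks the questions.

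If the two kinds of assessor obtain different answers at 12 months for the same true state, the difference enters the estimated intervention effect. The outcome at stake is the one that shows whether participants have begun or made a change, which is central to an intervention built on the Transtheoretical Model.

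**Working it through.** **Side by side.**
- Primary outcomes (Mediterranean diet, physical activity, smoking): Table 4 gives all three to the external unit, with no split by arm.
- EuroQol-5D and the clinical measures: external unit, no split by arm.
- Stage of change: PHC professionals in one arm, external unit in the other, at both time points. It is the only participant effectiveness outcome in Table 4 divided in this way.
- No duplicate rating, calibration between assessors or assessor adjustment is described.
- Table 4 does not say whether the individual who treats a participant also scores that participant, only that the rater comes from the same staff group.

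**What can and cannot be separated.** Let Z be arm (1 = intervention) and A assessor (1 = PHC professional). By Table 4, A = Z for every record at both times. Let d be the true effect at 12 months, and b0 and b12 the scoring difference between professionals and the external unit at baseline and at 12 months.
- Expected arm difference at baseline, given randomised centres: 0 + b0
- Expected arm difference at 12 months: d + b12
- Difference in change: d + (b12 − b0)

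If b12 = b0, the bias is zero: an assumed 5 points at both times gives 5 − 5 = 0. If an assumed 4 points at baseline becomes 8 at 12 months, the bias is 8 − 4 = 4 points. The term b12 − b0 is an assessor-by-time effect. Since A = Z, its column in any model is identical to the arm-by-time column that carries d. The hierarchical models in the Analysis section cannot split the two, and no other model for these data could.

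**How much a net shift would matter (illustration).** The documents give no size for b12 − b0, so every shift below is an assumption. Inputs from Sample size: 1820 per arm, 13 centres per arm, 30% loss, intracluster correlation 0.01 (stated for the primary composite and borrowed here).
- Completers per arm: 1820 × 0.70 = 1274
- Completers per centre: 1274 / 13 = 98
- Design effect: 1 + (98 − 1) × 0.01 = 1.97
- Effective number per arm, n: 1274 / 1.97 ≈ 647

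With no true effect, true proportion p, and net upward shift b in the intervention arm, let q = p + b and m = (p + q)/2. Then se0 = √[2m(1 − m)/n], se1 = √[(p(1 − p) + q(1 − q))/n], and the two-sided 5% test rejects with probability Φ[(b − 1.96·se0)/se1] + Φ[(−b − 1.96·se0)/se1].

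For example, p = 0.30 and b = 0.05 give se0 ≈ 0.0260 and se1 ≈ 0.0260. The first term is then about 0.48 and the second is negligible.

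| Assumed net shift | False-positive rate, p from 0.20 to 0.50 |
|---|---|
| 2 points | 11-14% |
| 4 points | 30-41% |
| 5 points | 44-58% |
| 8 points | 82-92% |

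These rates apply to a comparison of 12-month proportions in which b is the part of the shift left after any constant component has been removed. A baseline-adjusted model has a somewhat different standard error, so they indicate scale only.

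**Is the remedy available?** Data collection and management has the external unit make two visits, at baseline and at 12 months, in each centre. A common assessor is therefore already on site in the intervention arm at both times.

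**The case against.** The strongest reply is that the same assessor is used at baseline and at 12 months within each arm, so a stable difference in scoring shows up at baseline and largely drops out. This stands. A reader might infer that any rater difference passes in full into the estimate, but the documents do not support that; only the part that arises or grows by 12 months does. The baseline difference is an imperfect guide even to the constant part, because it also contains chance imbalance between 13 centres per arm.

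Second, stages are defined in Table 1 by intention and time windows, so they are structured participant reports rather than free judgements. This limits the rater's discretion. It does not remove the pull towards giving one's own clinician an agreeable answer.

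Third, professionals need the stage to choose the intervention. This is true, but tailoring does not require that the same score serve as the outcome.

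Fourth, an analysis plan that is not shown might deal with it. It could specify baseline adjustment, but it cannot recover a common assessor that was never used.

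Fifth, a reader might set a plausible rater shift beside the 8% difference under Sample size. That figure concerns positive change in one or more of the three behaviours, a different outcome collected by the external unit in both arms. It is no yardstick here.

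Finally, a reader might infer that blood pressure and the professionals' own behaviours share the fault. They do not. The blood pressure wording applies alike to both arms, and the professionals' behaviours come from a self-administered questionnaire. Neither has an assessor that depends on arm.

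**Conclusion.** The point holds for one of the 18 listed secondary outcomes. For the proportion in action, maintenance or termination, assessor is fully confounded with arm in an unblinded trial. A constant rater shift would largely cancel under baseline adjustment. A shift that develops by 12 months, after the professionals have treated the participant, would bias the estimate by its full net amount and could not be separated from the intervention effect. Neither the size nor the direction of such a shift can be known from the documents; the rates in the table rest on assumed shifts, assumed proportions and a borrowed intracluster correlation.

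It would be wrong to infer that the main result is compromised. The three primary outcomes and EuroQol-5D are collected by the external unit in both arms, and the sample size does not rest on stage of change.

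Two lesser and separate points remain. The blood pressure wording under the secondary outcomes and the assignment in Table 4 do not clearly agree on who takes the measurement. The professionals' behaviour outcome is confined to intervention centres, although the questionnaire appears to go to professionals generally: only the extra appropriateness and acceptability items are restricted ("In addition only in health professionals of intervention centres, it includes nine items"). That control professionals complete the behaviour questions is the natural reading, but it is not stated outright.

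**What to change.** In Table 4, make the external unit responsible for scoring stage of change in both arms, with the same items, at its existing baseline and 12-month visits. State under the secondary outcome that this score defines it. Keep the professionals' rating in the intervention arm as a tool for tailoring only.

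The cost is a few extra items for intervention-arm participants at visits that already take place, using items the external unit already asks in the control arm. Some participants will be staged twice. The change equalises the assessor but does not make the assessment blind. If it can no longer be made, the comparison should be reported as confounded by assessor.

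Separately, reconcile the two statements on blood pressure so that one source and one responsible party apply in both arms. If control-centre professionals do complete the behaviour questionnaire, define that outcome as the change compared between intervention and control centres rather than before and after in intervention centres alone. Both are wording changes.
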